### Standardization and Calibration

Clinical examinations using the ICDAS codes and criteria will be performed among children with active dental caries by the primary investigator and the supervising staff (guide). Standardization and calibration for the ICDAS index will be done before commencing the study. Calibration will be done at the Department of Public Health Dentistry. For this, 10 participants will be chosen in the 4- to 6-year age group with dental caries with an ICDAS code of 1 or greater, for whom the examiners will record the index. For determination of intra-examiner variability, these participants will be recalled on different days and the same examiner will repeat the examination. Interexaminer reliability will be assessed and compared with the gold standard examiner (guide). The κ coefficient value will be calculated, and a κ coefficient of 0.80 and above will be accepted as a reliable level of agreement.

### Statistical Power

The sample size was calculated with G*Power (version 3; Universität Düsseldorf). Based on the results of Aly and Yousry [18], at a 5% level of significance and 95% power with an effect size of 1.594, (calculated by considering that the mean lightness value of one group was 71.3, SD 14.2 and the other group was 53.6, SD 6.7), and the primary end point being an evaluation of the staining propensity of SDF+KI at the end of 1, 3, and 6 months after treatment, with a 95% chance of detecting an increase in the mean lightness value from 53.6 in the control group to 71.3 in the experimental group, the minimum sample size in each group is 16. The expected dropout rate is 10%, so after considering the dropout rate, the sample size in each group is 30. Thus, the total sample required for the intervention will be 60 children (N=60).

For the secondary objective, with a significance level of 5%, a power of 80%, and an estimated critical *Z* value of 3.193, the study required 48 teeth, or 24 teeth per group. Finally, assuming 40% loss to follow-up, a sample size of 34 teeth was gathered in each group [19] to evaluate the caries-arresting effect of SDF+KI in the treatment of carious primary teeth at 6 and 12 months after treatment.

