**Methods:**

This study is a randomized controlled trial. A total of 60 children with caries that meet the criteria of the International Caries Detection and Assessment System (code 1 or above) will be randomly assigned to treatment groups, where group 1 will be treated with SDF and group 2 will be treated with SDF+KI. Discoloration of treated lesions will be assessed digitally using a Nix Mini color sensor. Participants will be followed up at 1, 3, and 6 months after treatment to digitally record the ∆L and ∆E values using the Nix Mini color sensor. Data will be analyzed using SPSS (version 28; IBM Corp). Independent sample *t* tests and the Mann-Whitney *U* test will be used to compare the 2 groups.

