### Phase 3: Follow-Up

#### Primary Outcome Measures

Staining propensity will be measured 1, 3, and 6 months after treatment. Evaluation of the change in color of the carious lesions will use photographs and the Nix Mini color sensor.

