### Data Analysis

Data will be analyzed using SPSS (version 28; IBM Corp). Descriptive statistics will include the mean and SD for continuous data and frequency and percentage for categorical data. An independent-sample 1-tailed *t* test or the Mann-Whitney *U* test will be used for comparing the 2 groups. *P* values will be considered statistically significant at ≤.05.

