## Discussion

### Principal Findings

Riva Star is a commercially available product that contains 38% SDF, so it will be used in the control group. Riva Star is the only commercially available product with 38% SDF+KI. As a result, it will be used in the case group. With oral administration, the average lethal dose (LD50) is 520 mg/kg. One drop (25 μL) contains 9.5 mg SDF, which is sufficient to treat 5 teeth. Considering that the smallest child with caries weighs around 10 kg, the dose would be 0.95 mg/kg. Hence, the relative safety margin for administering a complete drop to a 10-kg child is 380 mg/kg, so for an LD50 of 0.95 mg/kg the dosage is 400 times the safety margin. The actual dose is likely to be significantly lower. The recommended limit is 1 drop (25 μL) for 10 kg of body weight at every treatment visit. The maximum applied dose for 3 teeth is 2.37 mg, which would allow for over 400 applications [21].

Silver ions in the SDF solution have the potential to darken the tooth structure. It has been proposed that the KI solution can react with SDF to generate a bright yellow solid product (silver iodide), which could reduce the excess free silver ions that cause the black staining. Despite the presence of brilliant yellow precipitates following KI application, staining of tooth surfaces was still observed in an SDF+KI treatment group in a previous investigation. While KI is anticipated to eliminate SDF staining, its effect has not previously been quantified [22].

Patients are concerned about the aesthetic appearance of a restoration. Rather than analyzing color variations with the naked eye, which is typically subjective, we will quantify color changes using smart device measurements incorporating artificial intelligence, as these are more precise and repeatable [23].The Nix Mini color sensor is a wireless colorimeter that uses artificial intelligence to measure the exact color of surfaces and communicates the digital color values through Bluetooth to a smartphone or tablet. The color sensor blocks out ambient light and provides its own calibrated light source using the industry-standard 45/0° measurement. The device provides color readouts in International Commission on Illumination L*a*b* (CIELAB) format and calculates color differences in ∆E2000 [10]. The Nix Mini color sensor will be used immediately following treatment. From the Nix Mini color data, ∆L and ∆E values will be recorded and compared among the groups.

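### The primary staining end point names no deciding visit or colour measure, so the stated 5% level is not guaranteed for the primary claim

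*Protocol article*

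**What the plan says.** The Statistical Power section gives "the primary end point being an evaluation of the staining propensity of SDF+KI at the end of 1, 3, and 6 months after treatment". Primary Outcome Measures repeats the visits: "Staining propensity will be measured 1, 3, and 6 months after treatment". That section names photographs and the colour sensor as the means of assessment, but no single colour value.

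The abstract's Methods paragraph shows what is recorded: "Participants will be followed up at 1, 3, and 6 months after treatment to digitally record the ∆L and ∆E values using the Nix Mini" sensor. The Discussion (Principal Findings) adds that ∆"L and ∆E values will be recorded and compared among the groups".

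Data Analysis says that a 1-tailed t test or a Mann-Whitney "test will be used for comparing the 2 groups", and that P "values will be considered statistically significant at ≤.05". It singles out no visit or measure.

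The power calculation was done "at a 5% level of significance and 95% power with an effect size of 1.594", from the assumption that "the mean lightness value of one group was 71.3, SD 14.2 and the other group was 53.6, SD 6.7". These are lightness values, not changes in lightness, and no visit is attached to them.

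**The concern.** The power calculation budgets one test at 5%. The end point as described yields three comparisons if one measure counts, and six if both do. The protocol does not say which comparison carries the primary claim, or what follows if the visits or measures disagree. A difference at one month that has gone by six months, or a difference in ∆E without one in ∆L, could be reported as the primary finding or passed over, and the choice could be made after the results are seen. The 5% level would then describe each test but not the claim.

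The second measure also raises a question of meaning. The Discussion says that the device calculates ∆E2000, a distance between two colours. A distance has no sign. The Introduction and Discussion say that KI forms a yellow silver iodide precipitate, while SDF stains black. Either change moves the colour away from its starting point, so a larger ∆E is not by itself evidence of a darker lesion.

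**Working it through.** **1. The plan's own figures.** Inputs from Statistical Power: means 71.3 and 53.6, SDs 14.2 and 6.7.

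- Pooled SD = √((14.2² + 6.7²)/2) = 11.10
- d = (71.3 − 53.6)/11.10 = 17.7/11.10 = 1.594, as stated

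The stated minimum of 16 per group is not reproduced for one t test at 5% and 95% power. The noncentral t distribution gives 10 per group one-sided and 12 two-sided. That is a separate matter. Here it matters only that the calculation covers a single comparison of lightness.

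**2. Number of comparisons.** Three visits × one measure = 3. Three visits × two measures = 6. Formal testing of the photographs would add to the count.

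**3. Chance of at least one false positive.** Two assumptions are needed, because the protocol supplies neither: that a positive result on any comparison may be claimed, and a common correlation ρ between the test statistics. With each of k tests one-tailed at .05 (critical value c = 1.645):

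- ρ = 0: 1 − 0.95^k
- ρ > 0: 1 − ∫ φ(u) [Φ((c − √ρ·u)/√(1 − ρ))]^k du

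| Assumed ρ | One measure, 3 visits | Two measures, 3 visits |
|---|---|---|
| 0 | 14.3% | 26.5% |
| 0.5 | 11.8% | 18.6% |
| 0.7 | 10.3% | 14.8% |
| 0.8 | 9.3% | 12.6% |
| 0.9 | 8.0% | 10.0% |
| 0.95 | 7.1% | 8.4% |

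The rate returns to 5% only at ρ = 1. Two-sided testing changes little: three visits at ρ = 0.95 give 7.3%. A simulation of six tests with separate correlations, 0.95 between visits and 0.9 between measures, gives 9.5% one-sided, close to the bottom of the right-hand column.

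**4. What the remedy costs in power.** The planned 30 per group less 10% dropout leaves 30 × 0.90 = 27. For a t test with 52 degrees of freedom, the noncentrality is 1.594 × √(27/2) = 5.86.

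| Test level | Power, one-sided | Power, two-sided |
|---|---|---|
| .05, one test | 99.998% | 99.99% |
| .05/3 = .0167, three visits | 99.98% | 99.95% |

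These figures assume that d = 1.594 holds for the chosen measure and visit. A change in lightness has its own SD, which the protocol does not give.

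**The case against.** The strongest reply is that lightness is already the implied primary measure. The power calculation is framed as detecting a higher mean lightness, and Primary Outcome Measures names neither ∆L nor ∆E. This has weight: it favours the three-comparison column over the six. It does not settle the visit, because the same sentence in Statistical Power spreads the end point over all three.

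A reader might infer that the protocol sets up six primary tests, any one of which wins, with an error rate of 26.5%. The text does not support that. It gives a type of test and a threshold, and states no success rule. The 26.5% also requires independence, which is implausible for repeated readings of the same lesions and for two measures that share the lightness difference.

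A reader might also infer that ∆E cannot be tested one-tailed because it has no sign. That goes too far. The hypothesis that total colour change is larger with SDF alone is directional and coherent. What stands is narrower: ∆E cannot separate black from yellow. Nor does the protocol say that the yellow precipitate persists to the follow-up visits.

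Finally, multiplicity handling and repeated-measures modelling are commonly left to an analysis plan that is not shown. Their absence is not the point here. The choice of primary variable and time point belongs in the protocol, and this one fixes a three-visit end point with a flat threshold.

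**Conclusion.** The point holds in limited form. Followed as written, the plan does not hold the primary claim at 5%, because no visit or measure decides it. If success at any visit can be claimed, the error rate is about 7% to 14% for one measure and about 8% to 26.5% if ∆E ranks equally with ∆L. Both the any-visit rule and the correlations (0.95 down to 0) are assumptions. Repeated readings of the same lesions make the lower part of each range more realistic, so the inflation is probably modest, but it is avoidable.

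∆E describes total colour change and is not suited to decide whether a lesion stained darker.

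It would be wrong to say that ∆L at six months underlies the power calculation. Its inputs are mean lightness values with no visit given, so the choice has still to be made.

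**What to change.** Before group data are analysed, name one lightness-based measure at one visit as the single primary outcome. Lightness at 6 months, the last staining visit, is one example. State whether it is L itself or the change in L, and align the power statement with that choice. Make the other visits and ∆E secondary, with ∆E described as total colour change. If all three visits must remain primary, keep one lightness measure and split alpha, .05/3 = .0167 at each.

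No new data or visits are needed, and on the stated effect size the planned sample is ample under either option. The cost is that differences in ∆E, and under the single-visit option those at the other visits, can no longer be claimed as primary. Enrolment began in October 2023 (Results), so this changes the primary end point of a running trial. It has to be a dated, documented amendment made without sight of results by group.

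### The effect size of 1.594 and the 95% power rest on mean lightness, but the colour outcome recorded and compared is change (∆L and ∆E), so the stated power does not describe the variables compared

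*Protocol article*

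**What the plan says.** The Statistical Power section works "at a 5% level of significance and 95% power with an effect size of 1.594", obtained by taking that "the mean lightness value of one group was 71.3, SD 14.2 and the other group was 53.6, SD 6.7". It describes the result as a 95% chance of "detecting an increase in the mean lightness value from 53.6 in the control group to 71.3 in the experimental group". It names the end point as "the primary end point being an evaluation of the staining propensity of SDF+KI at the end of 1, 3, and 6 months after treatment". It then states that "the minimum sample size in each group is 16", and finally: "The expected dropout rate is 10%, so after considering the dropout rate, the sample size in each group is 30".

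The outcome text uses a different scale:

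- The Abstract (Methods) has children followed up at 1, 3 and 6 months "to digitally record the ∆L and ∆E values using the Nix Mini color sensor".
- Method of Application has ∆L and ∆E measured three times by one operator and averaged.
- Primary Outcome Measures describes the outcome as the change in colour of the lesions.
- Principal Findings (Discussion) says that ∆"L and ∆E values will be recorded and compared among the groups".
- Strengths and Limitations repeats that ∆L and ∆E are recorded.

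Data Analysis specifies a 1-tailed independent-samples t test or the Mann-Whitney U test, without saying which colour variable it applies to. The article gives no expected difference or SD for ∆L or ∆E. Nowhere does it name absolute L* as the variable compared.

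**The concern.** L*, ∆L and ∆E are three different variables. L* is a reading at one time. ∆L is the difference between two such readings, so its SD also depends on the spread of starting lightness and on the correlation between the two readings. ∆E (∆E2000 in the Discussion) is an overall colour difference that combines lightness with other colour components. An effect size computed from two lightness means cannot simply be carried over to the other two.

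The reference for ∆L matters as well. Method of Application mentions determining the initial shade of the lesion, but places this after the post-treatment photographs. The Discussion says the sensor is used immediately after treatment. If the reference is read before treatment, ∆L measures staining. If it is read afterwards, ∆L measures later drift, and the 17.7-point difference need not apply.

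Three things are at stake: whether the power claim supports the comparison that will be reported, whether precision is lost to variation in starting colour (eligibility begins at ICDAS code 1 with no stated upper code), and whether the choice among L*, ∆L and ∆E stays open until the data are in.

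**Working it through.** **Inputs from the Statistical Power section:** means 71.3 and 53.6, SDs 14.2 and 6.7, 5% significance, 16 per group as the minimum, 30 per group planned, 10% dropout (30 × 0.9 = 27). **From Data Analysis:** a 1-tailed test.

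**Inputs assumed, because the article does not give them:** baseline SD of L* of 6.7, 11.1 or 15; correlation rho between baseline and follow-up L* of 0 to 0.7; reference reading before treatment.

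**Step 1: the plan's own figure.** Pooled SD = sqrt((14.2² + 6.7²)/2) = sqrt(123.26) = 11.10. Effect size = (71.3 − 53.6)/11.10 = 17.7/11.10 = 1.594. This reproduces, and it shows that 1.594 is a standardised difference between two lightness means. The minimum of 16 does not follow from 95% power: the t test needs 12 per group two-sided or 10 one-sided, and 16 gives 99.2% two-sided. Nor does 10% dropout turn 16 into 30 (16/0.9 = 17.8, so 18). Those are separate matters. They bear on this point only because 30 per group leaves a large reserve.

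**Step 2: expected difference in ∆L.** With a pre-treatment reference, randomisation makes the expected baseline means equal, so the expected group difference in ∆L is still 17.7. Only the SD changes.

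**Step 3: SD of ∆L.** In each arm, Var(∆L) = SD_follow-up² + SD_base² − 2 × rho × SD_follow-up × SD_base, averaged over the two arms. Worst case (baseline SD 15, rho 0): arm variances are 201.64 + 225 = 426.64 and 44.89 + 225 = 269.89; the average is 348.27, SD 18.66, effect size 17.7/18.66 = 0.95.

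**Step 4: power for ∆L** (noncentral t, 5%):

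| Baseline SD | rho | SD(∆L) | Effect size | 16/group, 2-sided | 27/group, 2-sided | 30/group, 2-sided | 27/group, 1-tailed |
|---|---|---|---|---|---|---|---|
| 6.7 | 0 | 12.97 | 1.37 | 96.2% | 99.8% | 99.9% | >99.9% |
| 11.1 | 0 | 15.70 | 1.13 | 87.0% | 98.2% | 99.0% | 99.3% |
| 15 | 0 | 18.66 | 0.95 | 73.8% | 92.8% | 95.1% | 96.4% |
| 15 | 0.3 | 15.94 | 1.11 | 85.9% | 97.9% | 98.8% | 99.1% |
| 15 | 0.5 | 13.84 | 1.28 | 93.8% | 99.6% | 99.8% | 99.9% |
| 15 | 0.7 | 11.35 | 1.56 | 98.9% | >99.9% | >99.9% | >99.9% |

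Put the other way, a difference of 17.7 keeps 95% two-sided power up to an SD(∆L) of 18.7 with 30 per group, or 17.7 with 27.

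**Step 5: precision against a baseline-adjusted comparison.** Adjusted variance = 123.26 × (1 − rho²). Worst case: 348.27/123.26 = 2.8. Best case on the grid (baseline SD 6.7, rho 0.5): average Var(∆L) = 98.1, and 98.1/(123.26 × 0.75) = 1.06. If ANCOVA uses one common slope although the arm SDs differ, the low end of the range falls to about 1.0; the high end is unchanged.

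**Step 6: ∆E.** The calculation cannot be done. The article gives lightness means and SDs only, and ∆E also depends on the other colour components.

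**The case against.** The strongest reply is that the mismatch has little practical effect. The trial enrols 30 per group and plans a 1-tailed test, and on that basis power for ∆L does not fall below 96% anywhere on the grid, even after 10% dropout. The worst cells need a baseline SD above both SDs in the Statistical Power section and no correlation between a lesion's starting and later lightness. This stands. A reader might infer from the 74% to 87% figures that the trial is underpowered. The documents do not support that, because those figures belong to 16 per group and a two-sided test, which is not the planned design.

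A second reply is that the protocol never makes absolute lightness the primary end point. This also stands: the end point is called staining propensity, and lightness is only the quantity used to size the trial. It would over-read the text to say that two primary end points are declared. The inconsistency is between the sizing variable and the variables recorded and compared.

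A third reply is that ANCOVA is a preference that an article may leave to the analysis plan. In part this stands. With a pre-treatment reference, an unadjusted ∆L comparison is unbiased under randomisation, so adjustment is a gain in precision and not the repair of a bias. What an analysis plan cannot settle is that the published power statement rests on a different variable from those the same article says will be compared.

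**Conclusion.** The point holds as an unsupported power statement and an inconsistent colour variable. It does not show a shortage of children.

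- **∆E:** the stated power has no basis.
- **∆L from a pre-treatment reference:** the 17.7-point difference carries over. Over baseline SD 6.7 to 15 and rho 0 to 0.7, power is about 95% or more two-sided at 30 per group, 93% or more at 27, and 96% or more with the planned 1-tailed test. Raw ∆L costs 1.06 to 2.8 times the variance of a baseline-adjusted comparison, with the smallest cost when baseline spread is small.
- **∆L from a post-treatment reference:** neither the 17.7 nor these powers apply, and the article leaves open which reference is meant.

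The ∆L results rest on assumed baseline SDs and correlations and on the cited lightness means and SDs being right for this population.

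**What to change.** Name one primary colour variable. The preferred choice is lesion L* at follow-up, compared between arms by ANCOVA with pre-treatment L* as covariate; the lightness assumption in the Statistical Power section then applies to the variable analysed. Treat ∆L and ∆E as secondary. State explicitly that the reference reading is taken before treatment, and bring Method of Application and the Discussion into line on this.

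If ∆L or ∆E is kept as primary, restate the power with an expected difference and SD on that scale, with their source.

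The cost is one additional model and a reworded power paragraph. No new equipment is needed, and a pre-treatment reading is already required if ∆L is to measure staining. Adjustment cannot be used for any child whose lesion has no such reading.

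### The caries-arrest sample size allows for 40% loss with 34 teeth per group, but keeping the required 24 needs 40

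*Protocol article*

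**What the plan says.** The Statistical Power section of the protocol article has two calculations. The first, for staining, leads to 30 children per group and 60 in all. The second is for caries arrest and is counted in teeth. It opens with "For the secondary objective, with a significance level of 5%, a power of 80%, and an estimated critical *Z* value of 3.193", continues that "the study required 48 teeth, or 24 teeth per group", and ends: "Finally, assuming 40% loss to follow-up, a sample size of 34 teeth was gathered in each group". The same sentence ties the 34 to the assessment of arrest at 6 and 12 months. The section shows no inflation formula and gives no arrest proportions.

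Two other places bear on the point. The inclusion criteria admit children with at least one active carious lesion, so a child may contribute one tooth or several. The Data Analysis section states: "An independent-sample 1-tailed *t* test or the Mann-Whitney *U* test will be used for comparing the 2 groups". That makes the general group comparison one-tailed, but the article does not link it to the arrest calculation.

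**The concern.** An allowance for loss should leave the required number once the loss has occurred. Here the requirement is 24 per group and the assumed loss is 40%, yet 60% of 34 is well below 24. The likely cause is a familiar slip: multiplying by one plus the loss rate when the requirement should be divided by one minus it. At small loss rates the two forms nearly agree. At 40% they are six teeth per group apart.

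Arrest is one of the stated objectives, and the article's conclusions present the project as improving appearance while the effect of SDF is kept. The arrest comparison has to carry the second half of that statement. If it has less power than stated, a real difference in arrest between the groups is more likely to be missed and read as no difference.

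**Working it through.** **Inputs, all from the Statistical Power section unless noted.** Required evaluable teeth: 24 per group (48 in all). Loss: 40%. Stated size after inflation: 34 per group. Significance level 5%, power 80%; sidedness is not given for this calculation, so both are shown. Children: 30 per group. Lesions per child: at least one (inclusion criteria).

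**Step 1, reproduce the plan's figure.** n × (1 + d) = 24 × 1.40 = 33.6, which rounds up to 34. From the total, 48 × 1.40 = 67.2, rounded up to 68 = 2 × 34. The factor 1.4 is inferred, since the text does not show it, but it gives the printed number exactly.

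**Step 2, the inflation that keeps 24.** n/(1 − d) = 24/0.60 = 40 per group, or 48/0.60 = 80 in all. This does not reproduce 34.

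**Step 3, what 34 delivers.** 34 × 0.60 = 20.4, so about 20 teeth per group. The largest loss that still leaves 24 is 1 − 24/34 = 29.4%.

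**Step 4, effect on power.** Without arrest proportions the 24 cannot be rebuilt, so it is taken as giving exactly 80% power. Power at n teeth per group is then Φ((z_α + 0.842) × √(n/24) − z_α).

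| Test | n = 20.4 | n = 20 |
|---|---|---|
| Two-sided, z_α = 1.960 | Φ(2.802 × 0.922 − 1.960) = 73.3% | Φ(2.802 × 0.913 − 1.960) = 72.5% |
| One-sided, z_α = 1.645 | Φ(2.486 × 0.922 − 1.645) = 74.1% | Φ(2.486 × 0.913 − 1.645) = 73.4% |

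A two-sided t-test version gives 72.1% at n = 20. As a check, every pair of arrest proportions on a 1% grid for which the usual two-proportion formula without continuity correction returns 24 was tried. Power at 20 ran from 72.1% to 73.8% two-sided and from 73.1% to 74.6% one-sided. The upper ends belong to pairs whose power at 24 is already a little above 80%, because the sample size is rounded up.

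**Step 5, the critical Z.** The 5% critical value is 1.960 two-sided or 1.645 one-sided. A Z of 3.193 has a two-sided p of 0.0014. The sum of the significance and power quantiles is 2.802 two-sided or 2.486 one-sided, so 3.193 is not that either. Read as a noncentrality value at 24 per group, it would give Φ(3.193 − 1.960) = 89% two-sided or Φ(3.193 − 1.645) = 94% one-sided, not the stated 80%.

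**Step 6, teeth available.** One lesion in each of 30 children gives 30 teeth per group. Reaching 34 needs 34/30 = 1.13 treated lesions per child on average; reaching 40 needs 40/30 = 1.33.

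**The case against.** The strongest objection is that the loss of power is conditional. The 24 cannot be verified, and the one effect-related number printed with it is itself doubtful. If 3.193 is a mislabelled noncentrality value, two-sided power with 20.4 teeth would be Φ(3.193 × √0.85 − 1.960), about 84%. If the 24 came from a continuity-corrected formula, uncorrected two-sided power at 20 would be 81% to 84%. This stands as a limit on the 73%. But the first reading contradicts the stated 80%, nothing in the text supports the second, and under neither does 34 leave 24 teeth after 40% loss.

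It can also be said that the figures belong to the study cited at that point, since the sentence is in the past tense. The same sentence, however, applies the 34 to this trial's arrest objective and its 6- and 12-month visits.

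A third objection is that 34 is not a cap and that children with several lesions may supply more teeth. That is possible, but the inclusion criteria guarantee only one lesion each, and a chance surplus would not correct the printed calculation. Several teeth from one child are also likely to be correlated, which lowers power further.

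Two stronger readings are tempting and should not be made. A reader might infer that the 10% dropout in the staining calculation contradicts the 40% here. The documents do not support that: the 10% applies to children for staining up to 6 months, the 40% to teeth for arrest up to 12 months, and a longer horizon with a different unit can justify a higher figure. A reader might also infer from 3.193 that the calculation was not run at 5%. The same sentence states 5%, so a mislabelled quantity is at least as likely.

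**Conclusion.** The inflation is wrong as written. Under the plan's own 40% loss, 24 evaluable teeth per group need 40 teeth per group, not 34. The shortfall is six teeth per group at the start and about four at analysis (24 against about 20). This rests only on the three printed numbers.

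The effect on power, from 80% to about 72% to 74%, holds only if 24 per group really gives 80%, and it treats teeth as independent. It should not be read as the known power of the trial. The critical Z of 3.193 is mislabelled or wrong; which of the two cannot be settled from the article.

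Severity is moderate. Arrest is a secondary objective, and the primary comparison, the randomization and the enrolment of 60 children do not depend on this figure.

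**What to change.** Restate the arrest paragraph in one of two ways:

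- Keep 34 teeth per group and state what it delivers: about 73% power at 40% loss if 24 gives 80%, or equivalently that 34 tolerates a loss of no more than 29%.
- Set the target at 40 teeth per group (80 in all), counted over all treated lesions in the 60 children, and state the assumptions: at least 1.33 treated lesions per child on average, and independent teeth.

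In either case, correct 3.193 or name the quantity that it represents. Giving the two arrest proportions behind the 24 in the same sentence would let a reader check it.

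The cost is one revised paragraph. It should not be assumed that the second option needs no more children. That depends on the number of lesions per child, which the article does not give but the baseline examinations will show.
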